### **3.2.2. Sampling**

The study will be of an experimental type, involving randomization at the village level. Five districts in the Savanes and Kara regions, representing a total of 273 villages, were initially selected using the criteria of poverty and malnutrition rates. Random distribution between the control group and the intervention group was stratified by district, and the village selection was proportional to each district’s population in order to reach a desired 4,800 children in the control group aged 24 months or younger. At the end of this process, 81 villages in total were placed in the intervention group. In order to balance the sampling at cluster level, 81 villages were selected from the remaining 192 and placed in the control group.

All pregnant women (from the third month of pregnancy onward) and children under 2 years old living in the selected villages will be enrolled in the program. The baseline and endline surveys will sample, respectively, children aged six to 59 months old and six to 30 months old who live in these 162 villages, as well as their mothers.

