## **3.2. Methodology**

### **3.2.1. Approach**

The framework for analyzing the program’s impact will be experimental: all villages in the study area (*n*=162) will be randomly assigned either to an intervention group or a control group. Over a period of 24 months, cross-sectional surveys of children aged six to 29 months and their mothers will be conducted in these villages; one survey will take place before the program begins (hereinafter referred to as “baseline”) and the second will be conducted at the program’s end (hereinafter referred to as “endline”). A difference-in-differences analysis will permit both to determine whether situational evolution between the baseline survey and the endline survey differs significantly between the intervention group and the control group, and to conclude what impact is attributable to cash transfers and/or the flexible conditions with which they are associated.

Rationale for selected impact evaluation design:

1. ***Repeated cross-sectional vs. longitudinal design*.** We propose to use a repeated cross-sectional survey design rather than a longitudinal design primarily because our previous experience has shown that usual delays in program roll-out and full implementation can have profound effects on the evaluation study cohort (e.g. children aging out of the “window of opportunity” for maximum nutritional impact of the intervention – see point 2 below), making the cohort unusable for assessing impact on age-sensitive outcomes such as child feeding practices or stunting. Additional constraints of longitudinal designs include the logistical complexity and related additional cost of tracking individual children over time, compared to sampling children of a given age in a repeated cross-sectional design. However, given that our team has extensive experience with both types of designs, we are open to discussions with UNICEF and the World Bank regarding alternative designs.

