Given the considerations outlined above, the duration of the program (30 months), and logistical considerations about sample sizes at particular age ranges, we propose sampling children six to 29 months of age at endline (two years after the baseline). Sampling the six-to-29-month age range is a compromise that takes into account a minimum program exposure of 12 months and first exposure to the program no later than six months of age. These criteria are based on the assumption that the main program intervention of cash transfers will begin immediately following the baseline survey and continue for 30 months, although at the time of the endline survey no child would have been exposed to the program for more than 24 months. Any delay in the start of cash transfers will have an impact on the age range of children to be sampled.

Table 1 below illustrates the age of first exposure, and duration of exposure of children of different ages, assuming a period of 24 months between baseline and endline surveys, and an immediate start to the cash transfer program after the baseline survey:

Table 1 : Program exposure of sample age range at endline

| **Age (mo)  at Endline** | **Age (mo) at First Exposure to Program** | **Age (mo)at Last Exposure to Program** | **Total Program Exposure (mo)** |
| --- | --- | --- | --- |
| 0 | -6 | 0 | 6 |
| 6 | -6 | 6 | 12 |
| 12 | -6 | 12 | 18 |
| 18 | -6 | 18 | 24 |
| 24 | 0 | 24 | 24 |
| 30 | 6 | 24 | 18 |
| 36 | 12 | 24 | 12 |
| 42 | 18 | 24 | 6 |
| 48 | 24 | 24 | 0 |
| 54 | N/A | N/A | 0 |
| 60 | N/A | N/A | 0 |

Extensive information will be collected at the levels of villages, households, mothers, and children, in order to:

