### **3.2.3 Sample size**

Sample size estimates are calculated based on changes in different impact indicators; HAZ and stunting and are based on the following principles:

- Using tests that compare means and prevalence between the two groups;
- Taking into account the design effect since randomization is carried out at the village level rather than individually;
- Using a conservative approach which consists of ignoring the fact that randomization is stratified by district;

The following parameters are fixed:

- 〈risk at 0.05;
- power at 90% ;
- 162 villages to be randomized (81 per group);
- Missing/invalid data at 10%;
- An intra-village correlation coefficient (ICC) that varies from 0.02 to 0.15

Based on the sample size estimates, we propose a sample size of 802 children aged six to 23 months/group, at baseline. This sample size will allow us to detect a difference of

9 points in prevalence of stunting and 0.20 in mean HAZ. This sample size will be extended to 1,020 children aged six to 29 months/group at baseline.

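### Section 3.2.2 sets the baseline survey at ages 6-59 months, sections 3.2.1 and 3.2.3 set it at 6-29, and nothing ties the difference-in-differences to one common age window

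*Protocol*

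**What the plan says.** Four statements in the protocol bear on the survey age window.

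- Section 3.2.1 (Approach), introducing the baseline and endline surveys together: "cross-sectional surveys of children aged six to 29 months and their mothers will be conducted in these villages".
- Section 3.2.1, at the end of the design rationale: "we propose sampling children six to 29 months of age at endline (two years after the baseline".
- Section 3.2.2 (Sampling): "The baseline and endline surveys will sample, respectively, children aged six to 59 months old and six to 30 months old".
- Section 3.2.3 (Sample size): first "we propose a sample size of 802 children aged six to 23 months/group, at baseline", then "This sample size will be extended to 1,020 children aged six to 29 months/group at baseline".

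Section 3.2.6 (Data analysis) estimates impact by difference-in-differences. The model displayed has phase, group and their interaction. Height-for-age z-score (HAZ) is the primary outcome. Section 3.2.6 does not say which ages enter the model at each round.

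**The concern.** Section 3.2.2 assigns a different window to each round explicitly, so its 59 does not read as a stray digit. It is also the section from which a field team would draw the sample. Section 3.2.1 treats stunting and feeding practices as sensitive to age and gives much of its rationale to choosing the age at measurement.

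The baseline contrast between arms is in the model to remove pre-existing differences in the population studied at endline. If it comes largely from children aged 30-59 months, it describes a different population and does that job less well. The phase coefficient, which the protocol reads as the change between surveys, would also absorb the change in age. The age composition of the baseline sample cannot be repaired after fieldwork.

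**Working it through.** **1. The windows side by side (completed months, inclusive).**

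| Section | Baseline | Endline |
|---|---|---|
| 3.2.1 | 6-29 | 6-29 |
| 3.2.2 | 6-59 | 6-30 |
| 3.2.3 | 6-29 (calculated for 6-23, then extended) | not stated |

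The baseline conflict is material. The endline conflict is one month and may be loose wording for under 30 months. In Table 1 of section 3.2.1, a child aged 30 months at endline is first exposed at 6 months, which is the limit that section sets.

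**2. Can the planned sample size be reproduced?** Not uniquely. The HAZ standard deviation, the control stunting prevalence and a single ICC are not given; for the last the plan has only "An intra-village correlation coefficient (ICC) that varies from 0.02 to 0.15". With two-sided alpha 0.05 (sidedness assumed), power 90%, a difference of 0.20, 81 villages per group and 10% loss:

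- n0 = 2 × (1.96 + 1.2816)² × SD² / 0.20²
- N = n0 × (1 − ICC) / (1 − n0 × ICC / 81) / 0.9
- SD 1.10, ICC 0.02: n0 = 636, N = 822
- SD 1.00, ICC 0.05: n0 = 526, N = 823

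The planned 802 is compatible with inputs of this kind, for a comparison of two groups at one time point.

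**3. Which ages does the 1,020 belong to?** Scaling 802 by months of age (uniform ages assumed) gives 802 × 24/18 = 1,069 for 6-29 months and 802 × 54/18 = 2,406 for 6-59 months. The planned 1,020 is close to the first and far from the second, which agrees with its label in section 3.2.3.

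**4. Section 3.2.2 followed without restriction (uniform ages assumed).**

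- Baseline months inside 6-29: 24/54 = 44.4%
- Baseline months at 30-59: 30/54 = 55.6% (29/54 = 53.7% if the endline runs to 30)
- Window midpoints: (6 + 60)/2 = 33 months at baseline; (6 + 30)/2 = 18 at endline, or 18.5 if it runs to 30

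**5. Effect on the estimate.** Both arms use the same window within a round, so the shift in mean outcome due to age falls on the phase coefficient and cancels from the interaction. Under randomisation the expected baseline contrast is zero in any age band. For precision, write V0 and V1 for the variances of the baseline and endline contrasts and r for their correlation through shared villages:

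Var(difference-in-differences) = V1 + V0 − 2r√(V0·V1)

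Baseline children of other ages can be expected to lower r. The protocol gives no r, so the loss cannot be sized.

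**6. What the wider survey would require.** Holding 1,020 per group aged 6-29 inside a 6-59 survey needs 1,020 × 54/24 = 2,295 per group, or 4,590 in all. Section 3.2.4 gives about 30 interviewers and 100-135 minutes per visit including measurement; section V gives about 45 days. That is 4,590/(30 × 45) = 3.4 visits per interviewer per day, or 5.7-7.7 hours, against 2,040/1,350 = 1.5 for a 6-29 survey. This assumes one visit per child, no rest days and no travel time. The protocol does not size such a survey.

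**The case against.** The strongest reply is that three of the four statements agree on 6-29 months and section 3.2.2 is the outlier. Villages are randomised, an age shift common to both arms does not enter the interaction, and HAZ is already standardised for age against the WHO 2006 reference. All of this stands, and it limits the harm to comparability, precision and the meaning of the phase term. It does not remove the contradiction, because no section says that the baseline is cut to the endline ages.

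A reader might go further and infer that matching ages would discard more than half of the baseline sample: 1,020 × 24/54 = 453 per group, or 408 after 10% loss. On a nominal 90% power, that would appear to leave about 75% (ICC 0.02) to 82% (ICC 0.10). The protocol does not support this, for two reasons.

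- Section 3.2.3 defines the 1,020 as children aged 6-29 months at baseline, so restricting a wider survey to those ages leaves them all in place.
- The 90% belongs to a two-group comparison with 802 per group, not to a difference-in-differences with 1,020. For HAZ 0.20, SD 1.1 (assumed) and ICC 0.02, ignoring correlation between rounds, the difference-in-differences has about 71% power before any age restriction.

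Even if the 1,020 were spread over 6-59 months, the standard error would rise by 10% (ICC 0.15) to 23% (ICC 0.02). In the same example, power would go from about 71% to 53%.

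The displayed model has no age term, but covariates are commonly left to the analysis plan, so that is not counted here.

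**Conclusion.** The point holds as an internal contradiction in the baseline age window (6-59 versus 6-29 months), together with the absence of any statement that the impact analysis uses one common age range. If section 3.2.2 is followed without restriction, about 56% of the baseline age range lies outside 6-29 months and the window midpoints differ by about 15 months. Both figures rest on the window widths; the share of children also needs uniform ages, which the protocol does not state. The consequence is a baseline contrast drawn largely from the wrong ages, some unquantified loss of precision, and a phase coefficient that mixes time with age. Systematic bias in the phase-by-group interaction is not shown. Loss of planned sample is not shown either. The one-month endline difference is minor.

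**What to change.** - Reconcile section 3.2.2 with sections 3.2.1 and 3.2.3.
- State one common window, 6-29 completed months, for the impact analysis at both rounds. Writing it in completed months also settles 29 versus 30.
- State that the 1,020 per group refers to that window.
- If children older than 29 months are surveyed at baseline for another purpose, say that they are additional to the 1,020 per group and excluded from the impact models on child outcomes.

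The cost is a text correction and an age filter in the sampling or analysis. No extra fieldwork is needed if the surveys are confined to 6-29 months. If the wider baseline is intended, its total size and field capacity need to be stated. The change should be made before the baseline sample is drawn.

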### **3.2.3 Sample size**

Sample size estimates are calculated based on changes in different impact indicators; HAZ and stunting and are based on the following principles:

- Using tests that compare means and prevalence between the two groups;
- Taking into account the design effect since randomization is carried out at the village level rather than individually;
- Using a conservative approach which consists of ignoring the fact that randomization is stratified by district;

The following parameters are fixed:

- 〈risk at 0.05;
- power at 90% ;
- 162 villages to be randomized (81 per group);
- Missing/invalid data at 10%;
- An intra-village correlation coefficient (ICC) that varies from 0.02 to 0.15

Based on the sample size estimates, we propose a sample size of 802 children aged six to 23 months/group, at baseline. This sample size will allow us to detect a difference of

9 points in prevalence of stunting and 0.20 in mean HAZ. This sample size will be extended to 1,020 children aged six to 29 months/group at baseline.

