### **3.2.6. Data analysis**

Statistical analyses will be performed using either R or STATA software. These analyses will take into account the characteristics of the sampling plan in strata (prefectures) and clusters (villages), and will be weighted according to village population sizes. The *p*-value, alpha, will be set at 0.05 and used as the threshold of significance for all comparisons.

Before the actual impact analysis, the results regarding indicators of interest will be presented by randomization group (intervention/beneficiary and control/non-beneficiary) at baseline in a descriptive fashion and by randomization group and prefecture at endline. Results concerning quantitative variables will be expressed in arithmetic mean values, while those dealing with qualitative variables will be expressed as frequencies (in percentages).

In order to evaluate program impact on the indicators of interest, the difference-in-differences method will be used. This method consists of comparing the intervention group to the control group both before and after the introduction of cash transfers. The underlying hypothesis is that absent the cash transfer program, the mean evolution of the indicators of interest should be the same in both groups. By considering an interaction term between the phase (baseline or endline) and the randomization group (intervention or control), this method permits evaluating whether the indicators’ evolution between the baseline and endline surveys differs significantly between the two groups. In other words, the difference-in-differences estimator compares the difference observed in the intervention group before and after program implementation with that observed in the control group. It also enables taking pre-existing differences between the intervention and control groups into account, as well as temporal effects, and thus allows for a conclusion on the existence of an impact attributable to cash transfers and/or the flexible conditionalities associated with them.

To this end, quantitative variable analysis will be conducted with the help of linear regression models, while qualitative binary variable analysis will be conducted with the help of logistic regression models. We will formulate
[figure not shown]

[figure not shown]
 (the estimation of the indicator of interest) and
[figure not shown]

[figure not shown]

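### The 90% power stated in section 3.2.3 is for a two-group comparison and is not justified for the difference-in-differences test planned in section 3.2.6

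*Protocol*

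**What the plan says.** Protocol section 3.2.3 opens with "Sample size estimates are calculated based on changes in different impact indicators" and names HAZ and stunting. The first principle it lists is "Using tests that compare means and prevalence between the two groups". It adds a design effect for villages and ignores the district stratification. The fixed inputs are alpha 0.05, power 90%, "162 villages to be randomized (81 per group"), "Missing/invalid data at 10" per cent, and "An intra-village correlation coefficient (ICC) that varies from 0.02 to 0.15". The result is "we propose a sample size of 802 children aged six to 23 months/group, at baseline", said to detect "9 points in prevalence of stunting and 0.20 in mean HAZ". The baseline sample is then extended to 1,020 per group aged 6-29 months, with no new power figure.

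Section 3.2.6 says: "In order to evaluate program impact on the indicators of interest, the difference-in-differences method will be used". The estimate is the coefficient of the phase-by-group product, in a linear model for HAZ and a logistic model for stunting. HAZ is the only primary outcome. Section 3.2.1 specifies repeated cross-sections rather than a cohort, and section 3.2.2 places both surveys in the same 162 villages.

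**The concern.** A two-group comparison carries the sampling error of one survey round. A difference-in-differences estimate subtracts the baseline group difference from the endline one. With different children in each round, the child-level error enters twice. Only the stable part of the village effect cancels.

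Section 3.2.3 lists no between-round term, no correlation of village effects over time and no endline sample size. Its power claim therefore does not carry over to the test in section 3.2.6. If power for the interaction is well below 90%, a true 0.20 HAZ effect would be missed more often than the stated one time in ten. A non-significant primary result could then be read as evidence of no effect.

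**Working it through.** **Inputs from the protocol.** Alpha 0.05 (taken as two-sided), power 90%, 81 villages per group, 10% loss, ICC 0.02-0.15, differences of 0.20 HAZ and 9 points of stunting. Evaluable children per group: 802 × 0.9 = 722, and 1,020 × 0.9 = 918.

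**Assumptions, not in the protocol.** HAZ SD (1.0 unless stated), the same n at endline as at baseline, and persistence c, the correlation of village effects between rounds, from 0 to 1.

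**Formulas.** With m = n/81 children per village and round:
- One round: V1 = 2·SD²·[ICC + (1 − ICC)/m]/81
- Interaction: V2 = 4·SD²·[ICC·(1 − c) + (1 − ICC)/m]/81
- Power = Φ(0.20/√V − 1.96); detectable difference at 90% power = 3.2415·√V

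**The plan's own figure.** It cannot be reproduced exactly, because the SD, control prevalence and ICC behind 802 are not given. The one-round formula comes close. With SD 1.0 and ICC 0.05 it needs 740 evaluable, or 740/0.9 = 823 enrolled, within 3% of 802. At 722 evaluable, V1 = 2·(0.05 + 0.95/8.91)/81 = 0.00387, SE = 0.0622 and power = Φ(3.216 − 1.96) = 89.5%. For 9 points of stunting at the same ICC, a control prevalence of about 32% gives 90%.

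**Which contrast fits 802?** At 722 evaluable, 90% power for 0.20 HAZ in one round implies an SD of 1.09, 0.99, 0.88 or 0.79 at ICC 0.02, 0.05, 0.10 or 0.15. Had 802 been computed for the interaction, the implied SD would be 0.56-0.77 with c = 0 and 0.84-0.90 with c = 1.

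**Variance ratio V2/V1 at 722 per round.** It is 2.00 at c = 0 for every ICC. At c = 1 it is 1.69, 1.36, 1.00 and 0.78 at ICC 0.02, 0.05, 0.10 and 0.15.

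**Anchored on exactly 90% in one round at 722.** With c = 0, interaction power is Φ(3.2415/√2 − 1.96) = 63%. Detectable differences become 0.20·√2 = 0.283 HAZ and roughly 9·√2 = 12.7 points of stunting (an approximation, since stunting is modelled on the log-odds scale). Moving to 918 in both rounds with c = 0 gives 67-72% across the ICC range.

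**SD fixed at 1.0: power for 0.20 HAZ (%), with the detectable difference in brackets.**

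| ICC | One round, 722 | Interaction, 722, c = 0 | Interaction, 722, c = 1 | Interaction, 918, c = 0 | Interaction, 918, c = 1 |
|---|---|---|---|---|---|
| 0.02 | 94.2 (0.184) | 70.4 (0.260) | 77.5 (0.239) | 78.8 (0.235) | 86.4 (0.212) |
| 0.05 | 89.5 (0.202) | 62.3 (0.285) | 78.7 (0.235) | 69.2 (0.264) | 87.5 (0.209) |
| 0.10 | 81.0 (0.228) | 51.9 (0.323) | 80.8 (0.229) | 56.5 (0.305) | 89.1 (0.203) |
| 0.15 | 72.9 (0.252) | 44.3 (0.357) | 83.0 (0.222) | 47.5 (0.342) | 90.8 (0.197) |

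**Sensitivity to SD, same formulas.** At SD 1.2, interaction power is 33-68% with 722 and 35-78% with 918. At SD 0.9 with 918, it is 91-93% at ICC 0.02 for c from 0.8 to 1.

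**The case against.** The strongest reply has four parts.

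- **The wording about changes.** Section 3.2.3 speaks of changes in indicators, so the calculation may already have been for the interaction. The wording is ambiguous, and a one-round calculation is an inference. But nothing listed under principles or parameters concerns a second round, and reading 802 as an interaction calculation needs a HAZ SD of 0.90 or less. On either reading, the section gives no basis for the interaction's power.
- **Same villages twice.** Stable village effects cancel. With 8.91 children per village and full persistence, the correlation of village means between rounds is ICC·m/[1 + (m − 1)·ICC] = 0.15, 0.32, 0.50 and 0.61 at the four ICC values. The interaction is then as precise as one round at ICC 0.10 and more precise at 0.15. This stands: doubling is the upper bound, not the expected result.
- **The operative sample is 1,020, not 802.** This also stands. If the SD is such that one round at 722 gives exactly 90%, the interaction at 918 reaches 90% for ICC 0.10-0.15 with persistence of 0.8 or more. It does not at ICC 0.02-0.05 for any persistence.
- **Not all of the shortfall comes from the interaction.** At SD 1.0 and 722 evaluable, one-round power is itself only 81% at ICC 0.10 and 73% at 0.15. This stands too, and is a further reason to restate the claim.

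The missing SD, prevalence and endline n could sit in an analysis plan and are not the complaint in themselves. The complaint is that the protocol states a power figure and names an estimator, and the two do not match.

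**Conclusion.** The stated 90% is not justified for the planned primary test. That follows from sections 3.2.3 and 3.2.6 side by side and needs no assumption about SD.

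The size of the gap does rest on assumptions. At SD 1.0, over ICC 0.02-0.15 and persistence 0-1, the interaction has 44-83% power for 0.20 HAZ with 722 evaluable per round, and a 90%-power detectable difference of about 0.22-0.36. With 918 evaluable the ranges are 48-91% and about 0.20-0.34. In the table, 90% is reached only at ICC 0.15 with full persistence and 918 evaluable.

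A reader might infer that the trial will fail to deliver 90% power, or that the variance will roughly double because each village contributes so few children. The document does not support either as a fact. SD, control prevalence, the ICC used, village persistence and endline n are all undocumented. Over much of the protocol's own ICC range, stable village effects could offset much or all of the penalty, and an SD near 0.9 with 1,020 per group can reach 90% when persistence is high.

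**What to change.** Recalculate section 3.2.3 for the phase-by-group contrast at the operative 1,020 per group. State the HAZ SD, control stunting prevalence, ICC, between-round village correlation and endline n used. Replace the 0.20 / 9-point claim with the power or detectable differences that result, shown over the stated ICC range.

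Alternatively, tie the 0.20 / 9-point claim explicitly to an endline comparison adjusted for baseline, check its power over the same ICC range, and make section 3.2.6 name that comparison as the one the sample size supports.

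Either route costs a recalculation and about one paragraph. No extra children are needed. The downside is that the stated figure will probably be less favourable.
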